## Abstract

**Background:**

Carotid artery stenosis or occlusion (CASO) is a major cause of vascular cognitive impairment (VCI). There is currently no effective treatment for VCI induced by CASO. Resveratrol, a type of polyphenol, improves cognitive performance in rat CASO models via pleiotropic effects. Furthermore, we previously reported the longevity gene, *SIRT1*, which can be activated by resveratrol, improves cognitive and cerebral blood flow impairment in mouse CASO models by activating endothelial nitric oxide synthase. However, clinical evidence remains limited.

**Methods:**

The REsveratrol for VAscular cognitive impairment investigating cerebral Metabolism and Perfusion (REVAMP) trial is a randomized, double-blind, placebo-controlled trial involving patients with asymptomatic CASO. Each participant will receive either 150 mg/day of resveratrol or a placebo for 35 weeks. The primary objective is to determine whether resveratrol improves cognitive impairment, as assessed using the Alzheimer’s disease Assessment Scale–cognitive subscale 13. One of our secondary objectives is to determine whether resveratrol improves cerebral hemodynamic impairment as assessed via ^15^O-gas positron emission tomography. We will recruit 100 patients (50 per group).

**Discussion:**

The REVAMP trial may provide valuable insights into new therapeutic options, as multitarget neuroprotection could potentially improve cognitive function along with enhancements in cerebral hemodynamic status in patients with asymptomatic CASO.

**Clinical trial registration**: The REVAMP trial was prospectively registered in the Japan Registry of Clinical Trials (jRCTs051230013) on April 13, 2023.

## Introduction

1

Carotid artery stenosis or occlusion (CASO), which can restrict cerebral hemodynamics, is an important cause of cerebral infarction and vascular cognitive impairment (1–4). According to the results of a meta-analysis encompassing 515 reports, it is estimated that patients with CASO aged 30–79 years make up 1.5% of the worldwide population, totaling approximately 57.79 million individuals (5). Asymptomatic moderate-to-severe carotid artery stenosis occurs in 4.2% of adults, with the prevalence increasing to 12.5% in men and 6.9% in women aged >70 years (6, 7). Furthermore, asymptomatic carotid artery stenosis impairs medication adherence, leading to failure of the primary prevention of ischemic stroke and vascular cognitive impairment (8). Consequently, the prevalence of asymptomatic CASO is higher, insidiously increasing the risk of vascular cognitive impairment, which suggests that asymptomatic CASO can no longer be considered truly asymptomatic but rather “symptomatic.” The undetected cognitive morbidity within such a substantial population carries potentially significant public health implications (2). However, preventive or therapeutic medication targeting vascular cognitive impairment with CASO has not been established.

Resveratrol (3, 5, 40-trihydroxy-trans-stilbene) is a type of polyphenol, which is naturally found in the skin of red grapes, red wine, blueberries, peanuts, and Japanese knotweed (9). It plays a key role in preventing various human diseases (including brain diseases) through its pleiotropic effects (10). Basic studies using rodent models have revealed that resveratrol improves cognitive performance in rat models of bilateral common carotid artery occlusion, which mimics chronic cerebral hypoperfusion. This improvement is achieved by decreasing oxidative stress, reducing inflammation, and promoting autophagy (11–13). Furthermore, resveratrol has been proven to cross the blood–brain barrier (14). We reported that the nicotinamide adenine dinucleotide (NAD^+^)-dependent longevity gene *SIRT1*, which can be activated by resveratrol (15), revealed improvements in cognitive performance and cerebral blood flow (CBF) via deacetylation of endothelial nitric oxide synthesis (eNOS) deacetylation in a mouse CASO model (16, 17). However, clinical evidence remains limited as there are only a few reports demonstrating positive effects on cognitive function in healthy subjects. In one study, the daily intake of oral resveratrol at a daily dose of 200 mg/day for 26 weeks significantly improved memory and hippocampal functional connectivity in healthy participants aged 50–75 years (9). Another study involving healthy postmenopausal women aged 45–85 years who received resveratrol at a daily dose of 150 mg/day for 14 weeks reported significant improvements in verbal memory and overall cognitive function (18). Long-term supplementation with resveratrol may be tolerable. Previous reports of resveratrol administration for 12 months have revelaed several adverse events, including exacerbation of gastric reflux, itching, menstrual changes, prolapsed bladder, and scheduled heart valve stent insertion and left eye operation. However, it is important to note that these events were not necessarily directly attributable to resveratrol supplementation at a dose of 150 mg/day (19, 20). Thus, the efficacy of resveratrol in patients affected by asymptomatic CASO remains unclear.

Before the start of the REsveratrol for VAscular cognitive impairment investigating cerebral Metabolism and Perfusion (REVAMP) trial, our preliminary retrospective observational study was conducted between July 2020 and March 2022 at the National Cerebral and Cardiovascular Center (NCVC) in Japan. The study involved 38 patients with asymptomatic CASO in the resveratrol-treated group and 44 patients with asymptomatic CASO in the nonresveratrol-treated group who underwent neuropsychological tests, such as the Alzheimer’s Disease Assessment Scale–cognitive subscale 13 (ADAS-Cog) (approval number of NCVC Research Ethics Committee: R20113). The mean observational period for the resveratrol-treated and nonresveratrol-treated groups was 223 ± 65 and 246 ± 87 days, respectively. We observed a significantly improved total ADAS-Cog score in the resveratrol group (−0.77 ± 1.88, 0.55 ± 1.74; *p* = 0.006) and an intergroup difference in the total ADAS-Cog scores of −2.35, calculated from the pooled variance estimates standard deviation of 3.86. Among the 82 patients, 79 underwent neuropsychological tests, such as ADAS-Cog and Montreal Cognitive Assessment (MoCA) and ^15^O-gas positron emission tomography (PET); 36 received resveratrol and 43 did not. Long-term resveratrol treatment significantly improved the memory domain and total score in the ADAS-Cog and the visuospatial/executive function in the MoCA. Furthermore, CBF improved in the anterior circulation territory and thalamus. No adverse events were observed (21).

Therefore, we hypothesized that long-term intake of resveratrol yielded beneficial effects on cognitive improvement accompanied by enhanced cerebral blood flow via pleiotropic effects such as activation of NAD^+^/SIRT1/eNOS axis, and decrease of oxidative stress and inflammation in patients with asymptomatic CASO. We aimed to prospectively determine whether the long-term clinical application of resveratrol at a daily dose of 150 mg improves cognitive impairment and the cerebral hemodynamic state, as assessed by ^15^O-gas PET, in patients with asymptomatic CASO. Herein, we provide a comprehensive description of the protocol for a clinical trial aimed at assessing the safety and efficacy of resveratrol administered at a daily dosage of 150 mg for patients with asymptomatic CASO.

## Methods and analysis

2

### Trial design

2.1

The REVAMP trial is an investigator-initiated, randomized, double-blind, placebo-controlled study that aims to investigate the safety and efficacy of the long-term intake of resveratrol 150 mg/day in patients with asymptomatic CASO and will be performed at the NCVC. One hundred participants will be randomly assigned to either the resveratrol or placebo control group in a 1:1 ratio (Figures 1, 2). During the REVAMP trial, participants will be given either resveratrol or a placebo for 35 weeks (Figure 3).

**Figure 1 fig1:**
[figure not shown]
Schematic flow diagram of the REVAMP trial’s participant enrollment process. ADAS-Cog, Alzheimer’s disease Assessment Scale–cognitive subscale 13; MoCA, Montreal Cognitive Assessment; PET, positron emission tomography; MRI, magnetic resonance imaging.

**Figure 2 fig2:**
[figure not shown]
The schedule of interventions and assessments of the REVAMP trial. PET, positron emission tomography; MRI, magnetic resonance imaging; AE, adverse events.

**Figure 3 fig3:**
[figure not shown]
Outline of the REVAMP trial. The schematic illustration was created with Biorender.com.

The physicians involved in the study will obtain written informed consent for the trial and the NCVC biobank from all trial patients before participating in the study. In case of any revision in the written informed consent form, the physicians involved in the study will explain the revised procedure again to the participants, revise the written informed consent form, and obtain the subject’s voluntary consent for continuation of participation.

### Study objectives

2.2

The primary objective will be change of ADAS-Cog total score from baseline to assess the effectiveness of resveratrol in preserving or improving cognitive function in patients with asymptomatic CASO. The principal secondary objectives will be to evaluate the impact of resveratrol on the following: (i) the preservation or enhancement of cognitive function, as evaluated by a change in the total MoCA score and the trail-making test score from baseline; (ii) the preservation or improvement of cerebral hemodynamic parameters, including CBF, oxygen extraction fraction (OEF), and cerebral metabolic rate of oxygen (CMRO_2_) as measured by ^15^O-gas PET (Table 1).

**Table 1 tab1:** Primary and secondary objectives.

Primary objective
Change of ADAS-Cog total score from baseline to 35 weeks.
Secondary objectives
1.Changes of MoCA total score and trail making test from baseline to 35 weeks. 2.Change of CBF examined by brain ^15^O gas-PET from baseline to 35 weeks. 3.Change of OEF examined by brain ^15^O gas-PET from baseline to 35 weeks. 4.Change of CMRO_2_ examined by brain ^15^O gas-PET from baseline to 35 weeks. 5.Volume or grade changes of white matter hyperintensities examined by brain magnetic resonance imaging (MRI) from baseline to 35 weeks. 6.Number changes of cerebral microbleeds examined by brain MRI from baseline to 35 weeks. 7.Change of systolic and diastolic blood pressure from baseline to 35 weeks.

### Inclusion criteria

2.3

The REVAMP trial will be conducted by investigators at the NCVC. We will include the following categories of participants: (i) patients aged ≥20 years and < 90 years at the time of consent; and (ii) individuals with asymptomatic carotid artery stenosis of ≥50%, or occlusion. A peak systolic velocity of ≥130 cm/s at a stenotic lesion, as measured by carotid Doppler ultrasonography, indicated a stenotic diameter of approximately ≥50% (22). The asymptomatic status will be confirmed based on the absence of stroke or transient ischemic attack caused by the development of a carotid lesion within 6 months (3). Patients with hypertension, cardiovascular diseases, or diabetes mellitus will not be excluded. Details of our eligibility criteria are presented in Table 2.

**Table 2 tab2:** Eligibility criteria.

Inclusion criteria
1.Patients aged ≥20 years and < 90 years. 2.Patients with asymptomatic carotid artery stenosis of ≥50% or occlusion. * Definition of ≥50% stenosis: 130 cm/s or faster of peak systolic velocity at a stenotic lesion examined by carotid ultrasonography. 3.Patients who gave their written informed consent.
Exclusion criteria
1.Severely demented patients who fail to undergo neuropsychological examinations. 2.Patients taking donepezil, galantamine, rivastigmine, or memantine. 3.Patients already diagnosed with secondary dementia (Parkinson’s disease, Huntington’s disease, normal-pressure hydrocephalus, progressive supranuclear palsy, multiple system atrophy, multiple sclerosis, head injury with sequelae, neurosyphilis, hypothyroidism, vitamin B1/B12 deficiency, and folic acid deficiency). 4.Patients with ≥50% stenosis or occlusion of the intracranial basilar artery and vertebral artery on brain magnetic resonance angiography. 5.Patients with a past history of intrinsic psychiatric disease or alcohol or drug dependence within 48 weeks before giving their informed consent. 6.Patients with severe pulmonary diseases (e.g., under home oxygen therapy). 7.Patients with a history of dose change in statins, PCSK9 inhibitors, intestinal cholesterol transporter inhibitors, and phosphodiesterase inhibitors within 4 weeks before giving their informed consent. 8.Patients who did not cease the intake of resveratrol or nicotinamide mononucleotide at least 4 weeks prior to the administration of the experimental drugs if the patients already consume resveratrol or nicotinamide mononucleotide. 9.Patients with severe renal dysfunction (eGFR <15 mL/min/1.73m^2^ or hemodialysis). 10.Patients who experienced malignancy within the past 5 years. 11.Pregnant and breastfeeding women or patients who do not agree to use appropriate contraception. 12.Patients participating in or planning to participate in other clinical trials using other medicines or medical devices.

### Screening procedures

2.4

Before enrollment, all potential participants will undergo an eligibility screening process by reviewing their medical charts to check the results of carotid ultrasonography. Personal information of potential and enrolled patients will be shared in a database accessible only within the project group to personnel responsible for patient inclusion, to protect confidentiality before, during and after the trial. At the first visit, the physicians involved in the study will provide detailed information about the REVAMP trial to the patients and/or their families and obtain written informed consent. Participants will be informed in the consent forms that they have the right to withdraw from the trial without any negative consequences. The attending physician will conduct a physical examination of all participants, and the clinical research coordinators (CRCs) will collect necessary clinical data such as height, body weight, vital signs, medical history, supplements, and demographics.

### Baseline assessments

2.5

After the initial screening, all participants will undergo neuropsychological assessments such as ADAS-Cog, MoCA, and the trail-making test. They will also undergo ^15^O-gas PET and brain magnetic resonance imaging, randomized at visit 2 (Figure 2). Blood samples for analyses will be collected before taking either resveratrol or placebo tablets and stored in the NCVC biobank. The tablets will be then distributed to participants after randomization (See the Randomization, allocation, and blinding section) by each physician involved in the study. To ensure proper medication adherence, all participants will be instructed to fill out a schedule book specific to the REVAMP trial every day and return the remaining tablets at each visit.

### Follow-up assessments

2.6

All participants will be required to visit the NCVC at weeks 12 and 35, which will be the final visit. During the week 35 visit, carotid ultrasonography, neuropsychological assessments, ^15^O-gas PET, and brain magnetic resonance imaging will be conducted, and blood samples will be collected and stored in the NCVC biobank. At weeks 12 and 35 (Figure 2), each physician involved in the study will conduct a physical examination, and the CRCs will conduct interviews to inquire about changes in prescription, over-the-counter medications and supplements, and occurrence of adverse events. To promote participant retention and complete follow-up, the CRCs will call the participants at least once a month to check whether the participants are continuing taking the resveratrol or placebo tablets.

### Randomization, allocation, and blinding

2.7

The physicians involved in the study will generate the allocation sequence, enroll patients, and assign patients to interventions. Registered patients will be assigned randomly to either the resveratrol group or the control group. The assignment method will be minimization, and the stratification factors considered will be sex, the presence of left CASO, and a total score of ADAS-Cog ≥15. The randomization process will be executed using computer-generated random allocation treatment codes. Both patients and physicians will remain blinded to the assigned therapy throughout the study. The randomization list will be maintained by an independent investigator who is not involved in patient care, assessment, data collection, or analysis. Emergency unblinding will only occur if the principal investigator deems it necessary to reveal the assigned intervention to manage any potential adverse events among participants.

### Interventions

2.8

Nature Holdings Co., Ltd. in Japan will supply standardized resveratrol and placebo tablets. The resveratrol tablets will be manufactured using 99% pure synthetic trans-resveratrol (resVida™, DSM Nutritional Products Ltd., Kaiseraugst, Switzerland), comply with Good Manufacturing Practice. The visual appearance of the placebo tablets was identical to that of the resveratrol tablets. Participants in the resveratrol group will be administered one 75-mg tablet of resveratrol twice daily (in the morning and evening) for 35 weeks. Conversely, those in the control group will receive one placebo tablet twice daily (also in the morning and evening) during the same period. Participants will consume one tablet with water. The physicians involved in the study or CRCs will maintain a comprehensive tablet inventory record, which will include information on the supply, receipt, disposal, and return of the trial tablets.

Discontinuance criteria will be as follows: (i) severe renal dysfunction (estimated glomerular filtration rate of <15 mL/min/1.73m^2^); (ii) severe gastrointestinal symptoms requiring emergent treatments; (iii) initiation of taking resveratrol or nicotinamide mononucleotide; (iv) initiation of taking antidementia drugs; and (v) administration of carotid endoarterectomy (CEA) or carotid artery stenting (CAS). Relevant concomitant care and interventions that are prohibited during the trial will be (i) resveratrol or nicotinamide mononucleotide; (ii) antidementia drugs; and (iii) CEA or CAS.

A restricted medication will be allowed if the doses are unchanged during the trial. Statins may improve anti-inflammatory, antithrombotic, and endothelial functions (23), and phosphodiesterase inhibitors may contribute to improvements in cerebrovascular regulation (24), potentially increasing CBF. Therefore, statins and phosphodiesterase inhibitors are included in the restricted medication list. Other medications or interventions may be used without restriction. Nonsteroidal anti-inflammatory drugs (NSAIDs) will not be included in the restricted medication list. NSAIDs used for <24 months do not affect cognitive function (25).

### Neuropsychological examination

2.9

Only psychologists who have substantial experience and are blinded to the intervention groups will be authorized to perform cognitive assessments, including ADAS-Cog, MoCA, and the trail-making test.

### ^15^O-gas PET measurements

2.10

All patients will undergo a series of ^15^O-gas PET examinations to assess CBF, CMRO_2_, and OEF. Radioactive ^15^O will be produced by accelerating a deuteron (d) beam via the 14 N (d,n) ^15^O nuclear reaction using a cyclotron (CYPRIS HM-12, Sumitomo Heavy Industry, Tokyo, Japan). Further, 0.3% oxygen (O_2_) in the nitrogen (N_2_) target will be used to produce the ^15^O–O_2_ and ^15^O–carbon monoxide (CO) gasses and 1.0% carbon dioxide (CO_2_) in the N_2_ target gas to produce the ^15^O–CO_2_ gas.

A PET scanner (Biograph mCT, Siemens Healthinier, Erlangen, Germany) will be used in the study. A PET scan was initiated 3 min after the 2-min inhalation of ^15^O–CO for 4 min. An additional dynamic PET scan was performed for 8 min during the sequential inhalation of ^15^O-O_2_ and ^15^O–CO_2_ gasses for 1 min each at a 4.5-min interval. The radiochemical purity was confirmed to be >99% before each radio gas inhalation in every patient via two-channel rapid gas chromatography (Micro 990, Agilent Technologies, Inc., Santa Clara, USA), as described in a previous study (26).

PET images will be reconstructed using vendor software, with an adequately selected methodology that considers the presence of gaseous ^15^O–radioactivity surrounding the face during images will require following the 2-min inhalation of the ^15^O–carbon monoxide gas (27). CBF and OEF images will be calculated using the previously validated dual-table autoradiography technique (28). Then, the functional images of CMRO_2_ will be calculated as follows:

$${\mathrm{CMRO}}_{2}=\left[O_{2}\right]a\times 1.39\times \%Sat\times Hb$$

[O_2_]a, the oxygen content in the arterial blood; %Sat, %saturation of oxygen in the arterial blood; Hb, the hemoglobin concentration in units of (mL/g); 1.39, the maximum amount of oxygen bound to the unit Hb mass (mL/min).

according to a previously validated technique (i.e., dual-table autoradiography technique) (28). The arterial input function will be obtained from the radioactivity concentration in the arterial blood that was continuously withdrawn from the brachial artery (28). The metabolized ^15^O-water in the arterial blood generated from ^15^O–O_2_ will be estimated by modeling physiological oxygen metabolism (29).

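### The printed CMRO2 equation, the only definition given for secondary endpoint 4, omits CBF and OEF, in effect counts arterial oxygen content twice, and gives two wrong units

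*Protocol article*

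**What the plan says.** Table 1 (section 2.2) lists as secondary objective 4: "Change of CMRO_2_ examined by brain ^15^O gas-PET from baseline to 35 weeks". Section 2.2 also names CMRO2 among the principal secondary objectives. Section 2.14 analyses its change by the same procedure as the primary endpoint.

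The only formula for CMRO2 is in section 2.10. That section first has CBF and OEF images produced by dual-table autoradiography. It then says that "the functional images of CMRO_2_ will be calculated as follows". The equation that follows is

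CMRO2 = [O2]a × 1.39 × %Sat × Hb.

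The legend gives [O2]a and %Sat as "the oxygen content in the arterial blood; %Sat, %saturation of oxygen in the arterial blood". Hb is the haemoglobin concentration, with the unit mL/g. The constant 1.39 is "the maximum amount of oxygen bound to the unit Hb mass (mL/min", so its printed unit is mL/min. After the legend comes a detached clause that attributes the calculation to the same validated dual-table technique.

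**The concern.** Every term on the right-hand side is an arterial-blood value or a constant. Nothing comes from the PET images, although the sentence promises an image and the two maps that could supply one have just been described. Three of the four factors also appear to rebuild the fourth.

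At stake is the definition of a principal secondary endpoint: the oxygen-metabolism measure in a trial whose name refers to cerebral metabolism and perfusion. Anyone who applied the printed line would be analysing a function of haemoglobin and saturation. A between-group difference in that quantity would say nothing about cerebral oxygen use, and a true effect on flow or extraction would not show in it.

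**Working it through.** **Inputs from the document.** The equation and its legend (section 2.10). The document gives no numerical result for CMRO2, so there is no figure to reproduce.

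**Inputs assumed for illustration.** Hb 0.14 g/mL (range 0.12 to 0.16); saturation 0.98 as a fraction (range 0.95 to 0.98); (CBF, OEF) pairs of (30, 0.40), (45, 0.40) and (30, 0.55), with CBF in mL/100 mL/min. None of these is in the document.

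**Step 1: what 1.39 × %Sat × Hb is.** By the legend's definitions:

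(mL O2 per g Hb) × (fraction saturated) × (g Hb per mL blood) = mL O2 per mL blood.

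This is the haemoglobin-bound oxygen content of arterial blood. It equals [O2]a if dissolved oxygen is ignored. The printed right-hand side is then [O2]a × [O2]a.

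**Step 2: dimensions.**
- By the definitions, the result is in (mL O2/mL)², with no time in it. It is not a metabolic rate.
- The printed units do not rescue it. With [O2]a as volume per volume, (mL/min) × (mL/g) gives mL²/(min·g), which is not oxygen used per unit tissue per unit time either.
- A concentration of Hb is mass per volume, and mL/g is the inverse. An amount of oxygen per unit Hb mass is mL/g, not mL/min.

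**Step 3: numbers.**

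[O2]a = 1.39 × 0.98 × 0.14 = 0.1907 mL O2/mL.

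Printed formula: 0.1907² = 0.0364, one value for the whole scan.

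The legend and the word order fit a two-equation reading: CMRO2 = CBF × OEF × [O2]a, with [O2]a = 1.39 × %Sat × Hb. It follows from what the terms mean: flow times arterial content is oxygen delivered, and the extraction fraction of that is oxygen used.

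| Assumed CBF, OEF | Printed formula | CBF × OEF × 0.1907 (mL O2/100 mL/min) |
|---|---|---|
| 30, 0.40 | 0.0364 | 2.29 |
| 45, 0.40 | 0.0364 | 3.43 |
| 30, 0.55 | 0.0364 | 3.15 |

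Over the assumed ranges of Hb and saturation, the printed formula runs from 0.025 to 0.048. The two-equation form runs from 1.90 to 3.92.

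**Step 4: sensitivity.**
- A 20% rise in CBF or OEF changes the printed formula by 0% and the two-equation form by 20%.
- A 5% rise in Hb changes the printed formula by 1.05² − 1 = 10.25%, because Hb enters directly and again through [O2]a. It changes the two-equation form by 5%.

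**The case against.** The strongest reply is that nobody will compute CMRO2 this way. The section has CBF and OEF images made first and places CMRO2 after them. It cites a validated technique and describes an arterial input function and an estimate of metabolized 15O-water. The operational method is the cited one, and the equation is a faulty summary of it. The line cannot yield an image at all, so anyone who tried to apply it would notice. This stands, and it limits the point. A reader might infer from the equation that the trial will fail to measure oxygen metabolism, but the document does not show that.

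A second reply is that a term or line may have been lost in typesetting or text conversion, since the clause after the legend is visibly stranded. This cannot be excluded. The legend lists exactly the four printed terms, which argues mildly against a loss. However, CBF and OEF are defined elsewhere in the article and need not have been repeated there. The wrong units stand in running text and are not explained by a lost term.

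A third reply is that an article condenses the full protocol. That excuses an omission, but here the article chose to state a formula and stated it wrongly.

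Finally, the form CBF × OEF × [O2]a is not printed in the document, so it has to be checked against the cited method. The numbers above rest on assumed blood values and do not measure any bias in the trial.

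**Conclusion.** The point holds as an error in the stated endpoint definition. The equation is wrong as written on its own legend, and no other section of the article gives a different one. Used literally, it would give one blood-derived number per scan that responds to haemoglobin and saturation and cannot respond to flow or extraction. That conclusion is algebraic. Only the reading as content squared needs an assumption, namely that dissolved oxygen is ignored.

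The likeliest explanation is two equations merged in drafting. This should be fixed, but it does not threaten the trial's main result. Section 2.14 judges efficacy on the ADAS-Cog analyses in the full analysis and per protocol sets, which do not use CMRO2. The sample size does not depend on it, and the CBF and OEF endpoints are not defined by this line.

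**What to change.** Correct the equation in section 2.10 to match the cited dual-table autoradiography method, in a form that uses the CBF and OEF images:

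CMRO2 = CBF × OEF × [O2]a, with [O2]a = 1.39 × %Sat × Hb.

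State Hb in g per unit blood volume, 1.39 in mL O2 per g Hb, and %Sat as a fraction. Rejoin the stranded clause to its sentence.

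Confirm and record that the PET processing code uses this form for both baseline and week-35 scans, so that the change score rests on one definition.

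The cost is a short correction to the text and a code check, with no new data and no change to the design or the analysis model.
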